## 5. STRATEGY

The HuCare Quality Improvement Strategy takes 16 weeks to complete (4 months); Figure 2 outlines its three phases:

### a) Clinician training

The medical and nursing staff of participating centers will attend an Evidence-Based Medicine (EBM) course (recommendation 1) [Fallowfield 2003, Brown 2008, McLeod 2014] to improve communication-relational skills and to receive instructions on how to enact the recommendations of the project (Attachment II). Considering an average of 8 oncologists and 14 nurses for each center (based on the HuCare study experience), 2 editions of the course for oncologists and 3 editions for nurses will be provided for each cluster group, during a period of 6 consecutive weeks. All editions will be held on weekends in Milan, at the AIOM HuCare School for Communication in Oncology located at Palazzo delle Stelline. Each center must ensure that at least 75% of medical staff and nursing staff operating in the ward complete training.

### c) Implementation of recommendations

Together with training (recommendation 1), 5 more recommendations for the psychosocial care of patients, identified in the HuCare project, will be implemented at each center by trained staff and with the support of the IT.

After the first visit with the oncologist, and before initiation of treatment, all “new” patients will receive the following activities, aimed to satisfy their information needs and to facilitate communication with the oncologist:

- The oncologist encourages the patient to use a question prompt list (recommendation 2), to favor communication. The tool was created in the framework of the HuCare project, by cross-cultural adaptation [Caminiti 2010] (Attachment III). The oncologist also introduces to each patient his or her specialist nurse (recommendation 3), who will accompany the patient through his/her care.
- The specialist nurse provides the patient with the two self-administered questionnaires, HADS and NEQ, validated into Italian (see paragraph 8), to detect psychological distress (recommendation 4) and social needs (recommendation 5). For patients with distress and/or social needs, necessary counselling and/or services (psychologist, psychiatrist, social worker, etc.) are activated, according to a written procedure defined at each center before the implementation phase begins. The specialist nurse also offers the patient a meeting at the Point of Information and Support (PIS), a space reserved for patients, equipped with internet access and information material. The PIS should be adjacent to the oncology offices, in a location ensuring privacy (recommendation 6).

## 6. OUTCOMES

The following secondary outcomes will also be assessed, again comparing baseline values with

measurements at 3 month follow-up up, during the post-intervention periods vs control periods, in order to test HQIS impact:

- in the long-term, i.e. whether different effects on patients initiating new treatment are detected over one year
- on global HRQoL, on specific scales and on individual symptoms, detected by the EORTC QLQ-C30 questionnaire
- on mood disorders, measured with the HADS-D scale
- according to patient subtypes with different baseline values of anxiety and depression [Zhu 2016].

To assess the actual degree of strategy's implementation at individual centers, the following secondary outcomes will be measured:

- percentage of clinical staff (oncologists and nurses) who complete training (see paragraph 5)
- percentage of patients with unmet social needs, detected with the NEQ (Needs Evaluation Questionnaire(see paragraph 8.1)) at baseline vs three-month follow-up
- percentage of eligible patients who receive HuCare recommendations, recorded during the implementation visit (csee paragraph 5 and Figure 2 ) on a sample of 5 consecutive cases for each center, by reviewing patients' clinical records where performed psychosocial interventions must have been noted.

## 7. TIMING

Patients will be screened and enrolled over 2 consecutive index weeks, to ensure necessary sample size and representativeness of different cancer types and treatments administered at the centers. Data collection will take place at two distinct time points:

- enrolment phase, when baseline patient data will be recorded
- assessment phase, when data for the same patients at 3-month follow-up will be recorded

| Timing                                                    | Epoch 1
From month 1 to 4 | Epoch 2
From month 5 to 8 | Epoch 3
From month 9 to 12 | Epoch 4
From month 13 to 16 | Epoch 5
From month 17 to 20 |
|------------------------------------------------------------------|-------------------------------------|-------------------------------------|--------------------------------------|---------------------------------------|---------------------------------------|
| Enrolment                                                 |                                     |                                     |                                      |                                       |                                       |
| Screening, Informed consent and Baseline questionnaire Cluster 1 | X                                   |                                     | X                                    | X                                     | X                                     |
| Screening, Informed consent and Baseline questionnaire Cluster 2 | X                                   | X                                   |                                      | X                                     | X                                     |
| Screening, Informed consent and Baseline questionnaire Cluster 3 | X                                   | X                                   | X                                    |                                       | X                                     |
| Intervention                                              |                                     |                                     |                                      |                                       |                                       |
| HQIS Implementation Cluster 1                                    | Control                             | Implementation                      | Post-Intervention                    | Post-Intervention                     | Post-Intervention                     |
| HQIS Implementation Cluster 2                                    | Control                             | Control                             | Implementation                       | Post-Intervention                     | Post-Intervention                     |
| HQIS Implementation Cluster 3                                    | Control                             | Control                             | Control                              | Implementation                        | Post-Intervention                     |
| Assessment                                                |                                     |                                     |                                      |                                       |                                       |
| Questionnaires at 3-month follow-Up Cluster 1                    | X                                   |                                     | X                                    | X                                     | X                                     |
| Questionnaires at 3-month follow-Up Cluster 2                    | X                                   | X                                   |                                      | X                                     | X                                     |
| Questionnaires at 3-month follow-Up Cluster 3                    | X                                   | X                                   | X                                    |                                       | X                                     |

**Table 1** –Data collection schedule

Effect measure at three months was chosen because QoL trend was observed to reach its negative peak 3 months after enrolment, and then to improve over one year [Aro 2015]. This trend may be explain by the adjustment trajectory of patients, who after an initial traumatic phase are able to adapt to the illness [Galway 2012]. Cocks et al. [Cocks 2012] also indicate 3 months as the ideal timing to use in studies measuring intervention impact on HRQoL, since it increases study efficiency (smaller sample size) given the wider difference between baseline and 3- months follow-up scores.

### **7.1 Eligibility assessment**

After the first consultation with the oncologist and before initiation of the first cycle of therapy, outpatients consecutively accessing the center will be screened by the oncologist over a period of two index weeks, indicated by the statistician. To this end, the oncologist checks the presence of all inclusion criteria and absence of all exclusion criteria, introduces the study to eligible patients, provides the information sheet and collects the informed consent to participation before initiation of the first cycle of therapy.

### **7.2 Baseline assessment**

Prior to initiation of the first cycle of therapy, and before implementing the recommended interventions addressed to patients, a specially trained research nurse of the center will enter demographic and clinical variables (taken from medical records) into the electronic data collection form (eCRF), and will instruct the patients on how to complete the questionnaires using a tablet. The time needed for completion is estimated not to exceed 20 minutes for each patient (12 minutes for the EORTC and 8 minutes for the other questionnaires). The research nurse will check completeness of entered information, and in the case of missing data will invite the patient to fill in the empty fields, noting any problems arisen in the process.

### **7.3 Three-month Assessment**

Before the medical follow-up appointment, the research nurse will invite the patient to complete the questionnaires using the tablet. At the end of the visit, the nurse will enter the following information taken from the clinical record into the eCRF: ECOG at 3 months, any disease progression (according to RECIST criteria), and any reasons for incomplete questionnaires and for the premature exit from the study (lost to FU, deceased, withdrawal).

## 8. STATISTICAL METHODS

Data will be processed with SAS software Version 8.2 (Statistical Analysis System) and STATA/SE version 11.0.

Before database lock and cleaning, the Statistical Analysis Plan (SAP) will be defined, comprising the following essential elements:

- Measure calculation and interpretation
- Statistical methods for the analysis
- Management of missing data
- Tables, lists and figures for data collection monitoring and for the final analysis.

### 8.1 INSTRUMENTS FOR OUTCOME MEASUREMENT

#### EORTC QLQ-C30

Quality of life, primary endpoint of the study, will be assessed with the validated Italian version of the European Organisation for Research and Treatment of Cancer Quality of Life Questionnaire-Core 30 items (EORTC QLQ-C30) [Apolone 1998], specific for patients with cancer. The tool is self-administered, and comprises 30 questions, 24 of which form nine multi-item scales representing the different aspects, or domains, of QoL: a global health status / QoL scale, five functional scales (physical, role, emotional, cognitive and social), and three symptom scales (fatigue, pain, nausea and vomiting), as well as 6 single items assessing additional symptoms (dyspnoea, loss of appetite, insomnia, constipation, diarrhea) and perceived financial impact of the disease).

As required in the Consort PRO extension [Calvert 2013], we briefly describe the ways the instrument and relative parameters for the assessment of the main endpoint were selected.

Various tools validated in many languages exist in the literature for the measurement of HRQoL, but two of them are most commonly used: the EORTC QLQ-C30 [Osoba 1994] and the FACT-G [Cella 1993] (Functional Assessment of Cancer Therapy-General). Luckett et al. [Luckett 2011] report an interesting comparison between the two tools, concerning content, scale, structure, psychometric properties, and other aspects, and constructed an algorithm which helps researchers in choosing the more adequate questionnaire according to the items of interest. Another recent work [King MT 2014] compares the two instruments' "responsiveness", or sensitivity to change, the most important property of a questionnaire used within a trial aiming to demonstrate the impact of an intervention, defined as the ability of an instrument to detect the minimal change considered to be clinically important by patients [Uwer 2011], and statistical efficiency, i.e. the sample size needed to detect such effects. Considering the nature of psychosocial interventions implemented in this study, which we hypothesize to mainly impact the social and emotional domains, and following the indications of the aforementioned papers, the QLQ-C30 was selected.

The choice of the three domains and corresponding timing, i.e. time point of effect measurement, was performed based on the analysis of the work by Cocks et al [Cocks 2012] with the aim to restrict assessment to the emotional and social functions which are mostly affected by the psychosocial intervention and to the population at greatest risk of QoL deterioration (patients during the first 3 months of treatment).

The questionnaire is self-administered using a touch-screen tablet device, at baseline and three months after enrolment, during the follow-up visit. The electronic version was chosen as it reduces completion times [Pollom 2015; Kesterke 2015] and the risk of missing data and entry errors [Marcano Belisario 2015], making QoL detection more efficient and accurate [Berry 2015]. Furthermore, the electronic

device for PRO detection has been shown to be easily used also by people over 70 years old, who only require a few more minutes than the younger population [Pollom 2015; Kesterke 2015].

To ensure the correct use of the questionnaire during data collection, as well as appropriate data analysis and interpretation, the indication of the EORTC manual will be followed.

### **Hospital Anxiety and Depression Scale**

The HADS is a self-report questionnaire, validated into Italian [Costantini 1999], comprising 14 items, 7 assessing the level of anxiety (HADS-A) and 7 assessing the level of depression (HADS-D), with scores for each item ranging from 0 to 3 and an overall score range between 0 and 42. For each statement, patients are asked to select among four options the one which best describes his/her emotional state referred to the previous week.

### **Needs Evaluation Questionnaire**

Social needs are detected using the NEQ, a tool developed in Italy, composed of 25 items, intended to record the main, potentially manageable social needs connected to the state of health, of patients with cancer [Tamburini 2000]. Identified areas concern information, communication and relationship with health care professionals; symptoms or functional difficulties; involvement of other professionals (social worker, psychologist, spiritual advisor); financial issues and help with lodging; psychological needs at an individual, family and social level.

## **8.2 Variable coding**

The following main patient demographic and clinical characteristics are collected at baseline to describe the study population and determine factors associated with quality of life:

- Date of birth (dd/mm/yyyy)
- Gender (M/F)
- Civil status (married or living with partner, other)
- Education (primary, high-school and above)
- Date of diagnosis (dd/mm/yyyy)
- Presence of metastases (yes/no)
- Cancer site
- ECOG performance status
- Type of treatment (IV chemotherapy , oral drugs, molecular target drugs)

At three-month follow-up, presence of disease progression will also be recorded (yes/no). For questionnaires where information was missing (less than half of items was completed), reasons for non-completion will also be noted, i.e. patient withdrawal, patient refusal to complete the item, worsening of patient's health conditions hindering completion, patient lost to follow-up or deceased (see paragraph 8).

As for coding of QLQ-C30 questionnaire variables, responses are given on likert scales and the sum of assigned values yields the score for each of the 15 domains. Highest values in the symptom domain (e.g. Diarrhea, weakness, vomiting etc.) will indicate severe symptomatology. Highest values in the other domains will indicate better quality of life. Scores of each domain are linearly transformed into a 0-100 scale, where 0 and 100 are assigned to the lowest and highest possible value, respectively.

For the HADS-D scale [Annunziata 2011] a cut-off of >7 will be used, a score considered clinically significant (i.e. patients scoring above this value may benefit from psychological support therapy) and with high sensitivity (0.86) and specificity (0.81) [Vodermaier 2011]. Missing values will be replaced with

the mean of the available values for anxiety or depression, if not more than four values are absent. The NEQ detects the presence of different types of needs using dichotomic choices (yes/no). It will enable to assess the frequency of needs and to compare it across the two detection periods (baseline and follow-up). Specifically, this information will allow to determine whether the HQIS is effective in reducing needs and whether this also corresponds to a positive effect on quality of life.

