## VALUTAZIONE BASALE – Depressione e ansia

|         |             |
|---------|-------------|
| Centro  | Paziente n° |
| □ □ □ □ | □ □ □ □     |

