## **REPORTING FORM**

### **Compilazione a cura dell'infermiere di ricerca**

**1. Se il paziente non ha compilato tutti e 3 i questionari o almeno uno dei questionari presenta meno del 50% degli item, indicare la motivazione:**

- ☐ Si rifiuta di completare il questionario [1]
- ☐ Le condizioni di salute non consentono di proseguire[2]
- ☐ Altro [3], specificare [3.1] \_\_\_\_\_

|                                                    |         |             |
|----------------------------------------------------|---------|-------------|
| VALUTAZIONE FOLLOW-UP – a 3 mesi dall'arruolamento | Centro  | Paziente n° |
|                                                    | □ □ □ □ | □ □ □ □     |

VALUTAZIONE DELLA QUALITÀ DELLA VITA CON EORTC QLQ-C30

VALUTAZIONE DELLA DEPRESSIONE E DELL'ANSIA CON HADS

VALUTAZIONE DEI BISOGNI PSICOSOCIALI CON NEQ

|                                                    |         |             |
|----------------------------------------------------|---------|-------------|
| VALUTAZIONE FOLLOW-UP – a 3 mesi dall'arruolamento | Centro  | Paziente n° |
|                                                    | □ □ □ □ | □ □ □ □     |

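### HADS-D is coded only as >7 versus ≤7 although the full 0–21 score is collected at both visits; if mood is analysed only in that form, precision is lost

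*Protocol*

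**What the plan says.** Protocol section 6 lists among the secondary outcomes the effect "on mood disorders, measured with the HADS-D scale", comparing baseline with 3 months in post-intervention and control periods. The synopsis words the same aim as a reduction of mood disorders, and section 2.2 as an effect on patient mood.

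Section 8.1 describes the instrument as having "7 assessing the level of depression (HADS-D), with scores for each item ranging from 0 to 3", so HADS-D runs from 0 to 21. The data collection form (Attachment IV) holds the whole HADS at baseline ("VALUTAZIONE BASALE – Depressione e ansia") and names it again among the 3-month questionnaires ("VALUTAZIONE DELLA DEPRESSIONE" and anxiety).

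Section 8.2 then fixes the coding: "a cut-off of >7 will be used". The support offered is clinical significance, in that patients above this value may benefit from psychological support, together with a sensitivity of 0.86 and a specificity of 0.81. The same section codes the QLQ-C30 domains differently, as scores on a 0–100 scale.

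**The concern.** The cut-off is justified by its accuracy as a screening threshold. That is a different property from sensitivity to change between periods, which section 8.1 treats as the most important property of a questionnaire in a trial of this kind when it explains the choice of the QLQ-C30.

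Under >7 versus ≤7, scores of 15 and 8 are coded alike, while 8 and 7 are coded differently. A real difference of seven points can therefore vanish, and a one-point difference at the threshold, which measurement noise could produce, changes the category.

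At stake is the chance of seeing an effect on mood if there is one. The protocol makes no power claim for this outcome, so no stated figure is wrong. The issue is precision given up on data that the trial already collects.

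**Working it through.** **Figures in the plan.** The protocol gives no sample size, power, prevalence, mean or SD for HADS-D, so there is no HADS-D figure to reproduce. The overall number follows from section 8.6: 3 clusters × 4 detection periods × 60 = 720. With the stated 20% drop-out, 720 × 0.8 = 576 patients would have a 3-month score. The design table has 6 control cells (1 + 2 + 3) and 6 post-intervention cells (3 + 2 + 1), so 6 × 60 × 0.8 = 288 patients per condition.

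**Assumed input.** Let p be the share of patients with HADS-D >7. It is not in the protocol and is varied from 10% to 50%.

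**Normal shift.** The efficiency of the split relative to the mean is φ(z_p)² / [p(1 − p)], where z_p is the normal quantile at p and φ the normal density. For example, at p = 0.20, φ = 0.280 and 0.280² / 0.16 = 0.49.

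**Proportional odds.** For a finely graded score the corresponding ratio is 3p(1 − p). At p = 0.20 it is 3 × 0.16 = 0.48.

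| Assumed share >7 | Efficiency, normal shift | Loss, normal shift | Loss, proportional odds |
|---|---|---|---|
| 50% | 0.637 | 36% | 25% |
| 40% | 0.622 | 38% | 28% |
| 30% | 0.576 | 42% | 37% |
| 20% | 0.490 | 51% | 52% |
| 10% | 0.342 | 66% | 73% |

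**Check on a discrete, skewed score.** Beta-binomial distributions on 0–21 with mean 4 to 7 and SD 3.5 to 4 (all assumed) put 16% to 42% of patients above 7. With the proportional-odds ratio for a discrete score, 3p(1 − p) / (1 − Σp_k³), where p_k is the probability of score k, the loss is 59% at the low end of that share and 27% at the high end. The order of magnitude therefore does not rest on normality.

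**What this means for power, patients treated as independent.** With 288 per condition, a shift of 0.233 SD gives the score 80% power at two-sided 5%. For the binary outcome the power is Φ[(Δ − 1.96·s₀)/s₁], with Δ the difference in proportions, s₀ its pooled standard error and s₁ its unpooled standard error:

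- From p = 0.50 the shift lowers the share to 0.408. Then (0.0923 − 0.0813)/0.0413 = 0.27, a power of about 60%.
- From p = 0.30 it lowers the share to 0.224, a power of about 54%.
- From p = 0.20 it lowers the share to 0.141, a power of about 47%.

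**Limits of the check.** These ratios compare two codings of the same patients. They contain no cluster effect, no period effect and no baseline adjustment, so they show the relative cost of the coding and not the power of this stepped-wedge design.

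**The case against.** The strongest reply is that section 8.2 is about coding, not analysis. It says that a cut-off will be used, not that it is the only or the main form of the outcome. Section 8 leaves the calculation of measures and the statistical methods to a SAP. The rule for replacing missing HADS items implies that scale scores will be computed. The cut-off may also have been meant for the patient subtypes by baseline anxiety and depression in section 6. Moreover, a reduction in mood disorders can fairly be read as a change in the proportion of patients in a clinical state, and for that question a threshold is a legitimate prespecified outcome.

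Much of this stands. A reader might infer that the protocol reduces the mood outcome to a dichotomy. The text does not go that far, because analysis of the score is nowhere excluded. A reader might also infer that a third to a half of the information is certainly lost, or that the 576 completers would act like 282 to 367. Those figures need an assumed share above 7 of 20% to 50%, a normal shift and independent patients, and the protocol supplies none of these. Nor is mood the leading secondary objective: it comes first in section 2.2, but last within objective (a) of the synopsis and third in section 6, and no hierarchy is stated.

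The reply does not remove the point. The >7 rule is a stated choice and the only HADS-D coding written down, in a section that gives a scale for the QLQ-C30. A SAP that follows section 8.2 would take it over. If the cut-off was meant only for screening or for subgroups, the protocol does not say so.

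**Conclusion.** The point holds in a conditional and modest form. The protocol fixes >7 versus ≤7 as the only coding of a score that it collects in full at both visits. If mood is analysed only in that form, the patient-level loss of information is about 36% to 66% under a normal shift as the assumed share above 7 falls from 50% to 10%, and about 25% to 52% under proportional odds as it falls from 50% to 20%. The size cannot be stated more tightly, because the protocol gives no HADS-D distribution, and clustering is ignored throughout.

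The consequence is limited to one secondary outcome without a power claim. The primary endpoint and the 720 patients are untouched. Using the score would not cure any weakness that comes from having only three randomised clusters.

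**What to change.** State in section 8.2 or 8.7, and carry into the SAP, that the main analysis of the mood outcome is the 3-month HADS-D score, adjusted for the baseline HADS-D score and fitted with the same model structure as the primary endpoint. The proportion of patients with HADS-D >7, by condition and period, is then reported as a supportive clinical summary. The rescaling in section 8.7 carries over directly with 0 and 21 as the lowest and highest scores. If the cut-off is also intended for screening or for the baseline subgroups, say so in the same place.

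The cost is a sentence or two of wording. No new data, visits or patients are needed. The one drawback is that the main estimate is less immediately readable than a proportion, which keeping the >7 summary offsets.

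### The NEQ is meant to show whether HQIS reduces needs, but the stated comparison is baseline versus follow-up with no control-period contrast

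*Protocol*

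**What the plan says.** Section 8.2 (Variable coding) explains that the NEQ records needs as yes or no. The frequency of needs is to be assessed and used "to compare it across the two detection periods (baseline and follow-up"), and "this information will allow to determine whether the HQIS is effective in reducing needs". The comparison and the conclusion drawn from it stand in consecutive sentences.

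Section 6 (Outcomes) has two lists of secondary outcomes. The first covers the long-term effect, the QLQ-C30 scales, HADS-D and patient subtypes. Its lead-in sets the contrast as "during the post-intervention periods vs control periods, in order to test HQIS impact". The second list has its own lead-in, "To assess the actual degree of strategy's implementation at individual centers, the following secondary outcomes will be measured", and contains the NEQ item: "percentage of patients with unmet social needs, detected with the NEQ (Needs Evaluation Questionnaire(see paragraph 8.1)) at baseline vs three-month follow-up".

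The synopsis also places unmet needs under implementation rate. Section 2.2 does not mention them. Section 8.7 states the post-intervention versus control contrast for the emotional and social domains only.

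**The concern.** The NEQ is classed as an implementation measure in the synopsis and section 6, and used for an effectiveness conclusion in section 8.2. In neither role is it given a control contrast.

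The baseline questionnaire is completed before the first cycle of therapy (section 7.2). Three months later the patient has been under treatment and in contact with staff. The NEQ asks about information, communication, symptoms, finances and psychological needs (section 8.1), any of which may shift over that interval with or without the strategy. A baseline-to-follow-up comparison cannot separate that shift from an effect of HQIS. An analysis that follows the text could report a reduction in needs when the strategy does nothing, or report no change when it helps. The randomised contrast, the reason for the stepped-wedge design, would go unused for an outcome measured under both conditions.

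**Working it through.** **1. What is compared and what is concluded**

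| Place | Comparison given | Purpose given |
|---|---|---|
| Section 6, first list (no NEQ) | post-intervention vs control periods | test HQIS impact |
| Section 6, second list (NEQ) | baseline vs three months | degree of implementation |
| Section 8.2 (NEQ) | baseline vs follow-up | whether HQIS reduces needs |
| Section 8.7 | post-intervention vs control | two HRQoL domains only |

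The effectiveness conclusion in section 8.2 has no controlled comparison behind it.

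**2. What each comparison estimates**

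Let m be the change in need prevalence over three months without the strategy, and h the effect of HQIS.

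- Before-after in post-intervention patients: m + h.
- Before-after in control patients: m.
- Difference, with calendar time handled by epoch terms: (m + h) − m = h.

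If h = 0, the first quantity equals m, and a fall in needs looks like benefit. If m = +10 points and h = −10 points, the first quantity is 0 and a real benefit disappears.

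**3. Whether the control data exist**

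The design table and section 8.6 give 60 patients per observed cluster-period.

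- Control cells: 1 + 2 + 3 = 6, so 6 × 60 = 360.
- Post-intervention cells: 3 + 2 + 1 = 6, so 6 × 60 = 360.
- Total 720, as stated. After 20% drop-out: 360 × 0.8 = 288 in each condition.

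Table 1 schedules baseline and three-month questionnaires in the control epochs too, and the follow-up form in Attachment IV includes the NEQ.

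**4. Illustration of size (assumed values)**

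The protocol states no figure for the NEQ, so there is none to reproduce. Assumptions: no HQIS effect; a single need with baseline prevalence p0 of 40, 50 or 60%; natural fall d of 0, 5, 10 or 15 points; within-patient correlation r of 0.3 or 0.5; n = 288; paired two-sided 5% test, normal approximation; clustering ignored.

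With p1 = p0 − d:

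- v = p0(1 − p0) + p1(1 − p1) − 2r√[p0(1 − p0)p1(1 − p1)]
- SE under the null = √[(v + d²)/n]; SE under the assumed change = √(v/n)
- Probability of significance ≈ Φ[(d − 1.96 × null SE) / SE]

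Example, p0 = 0.5, d = 0.10, r = 0.3: v = 0.25 + 0.24 − 0.147 = 0.343. Null SE = √(0.353/288) = 0.0350. SE = √(0.343/288) = 0.0345. Then (0.10 − 0.0686)/0.0345 = 0.91, and Φ = 0.82.

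| Natural fall | Probability of a significant change with no HQIS effect |
|---|---|
| 0 points | 5% |
| 5 points | 30 to 42% |
| 10 points | 82 to 94% |
| 15 points | 99% or more |

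The same range holds for a natural rise: exchanging need and no need turns a rise from p0 into a fall from 1 − p0, and the set 40, 50, 60% maps onto itself. If change varies between clusters, the effective sample is smaller and a test allowing for this would reject less often.

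**The case against.** Section 8.2 concerns coding, names no test or model, and does not say the control periods are excluded. Section 8 leaves statistical methods to the SAP. The protocol also uses baseline and follow-up as shorthand elsewhere: section 2.1 describes the primary endpoint as detected at those two times, although the contrast there is plainly HQIS versus standard care, and the first lead-in of section 6 combines both layers. The authors may have intended the same for the NEQ. As a descriptor of implementation, a before-after percentage is not wrong in itself.

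Part of this stands. The intention may be sound, and the choice of model belongs in the SAP. But the protocol is not silent: it names a comparison and an inference, and the one does not support the other. The lead-in with the control contrast governs a list that does not contain the NEQ.

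A reader might infer from section 7, which speaks of patients "who after an initial traumatic phase are able to adapt to the illness", that needs fall unaided and that the error favours HQIS. The text does not support that. It concerns quality of life, not needs, and puts the low point at three months with improvement afterwards. If needs followed that course, a masked benefit would be the likelier error. The direction is open.

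**Conclusion.** The point holds as a mismatch between a stated comparison and a stated conclusion. Baseline versus follow-up on the NEQ cannot show whether HQIS reduces needs, because it mixes any effect with change that would occur anyway. The bias may run either way, and the documents give no figure for it. The range of about 30% to over 99% rests on an assumed natural change of 5 to 15 points and the other assumptions listed. It shows that modest change is enough to matter; it is not an estimate for this trial.

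A reader might also infer that the trial's main conclusion is at risk or that the data are inadequate. Neither follows. The outcome is secondary, the primary analysis has its own control contrast, and the NEQ is collected under both conditions. The correction should be made, but it is not critical.

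**What to change.** In sections 8.2 and 6, state that any conclusion on HQIS and needs rests on the difference between post-intervention and control periods in three-month need frequency, adjusted for baseline NEQ and epoch and accounting for clustering. Use a model suited to yes/no data, for example a mixed logistic model; the beta-binomial model in section 8.7 is set up for scaled scores and does not carry over directly. Keep the baseline and follow-up frequencies as description, shown separately for control and post-intervention periods. If the NEQ is to serve both as an implementation measure and as an effectiveness outcome, say so in both sections.

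Epoch terms are needed because control cells lie in epochs 1 to 3 and post-intervention cells in epochs 3 to 5, so a pooled comparison would be confounded with calendar time.

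The cost is a few sentences of wording and no new data. The price is precision: only epoch 3 has both conditions side by side (cluster 1 post-intervention, cluster 3 control), so the adjusted estimate will be less precise than 288 versus 288 suggests. Details of the baseline adjustment can be left to the SAP.
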